### Assessment of safety and criteria for study discontinuation

The management of AEs that occur during this clinical trial will be in accordance with the guidelines of the approving Human Research Ethics Committee.

A safety analysis will be performed by a safety monitoring board that includes an independent orthopaedic field expert when 50% of the participants (58) reach the primary endpoint, at 12 weeks after TKA.

The primary criteria for discontinuation of the study will be poor outcomes, indicated by ROM. If > 18 participants (30%) in the experimental group (MAXM Skate program) present a ROM of < 90° at six weeks after TKA [40], the study will be discontinued. ROM assessments performed at six weeks will be conducted by both the study Physiotherapist at the six-week functional follow-up visit (specific to the study), as well as the treating orthopaedic surgeon at the routine six-week follow-up visit (routine clinical care at six weeks).

### Data management

Clinical study data will be recorded directly on the Case Report Form (CRF) and will be completed for each participant enrolled into the clinical study. The Principal Investigator or nominated Co-Investigator will review, approve and sign/date each completed CRF series, attesting to the accuracy and authenticity of the data entered.

Clinical study records will be filed in the Clinical Study Master File in an organised way that will facilitate management of the clinical study, audit and inspection. The files will be retained securely before archive and then archived for a period of not less than 15 years to allow for audit and inspection by regulatory authorities upon request.

The Principal Investigator will permit direct access of the study monitors, the appropriate Human Research Ethics Committee and appropriate regulatory authorities to the study data when required.

### Ethics and dissemination

This study received ethical approval from The Bellberry Human Research Ethics Committee on 24 September 2018. Any approved amendments made to the study protocol will be updated on the trial registry and the Therapeutic Goods Administration Clinical Trial Notification record, if appropriate.

Throughout the trial, investigators will endeavour to present preliminary findings at national and international orthopaedic conferences. At the conclusion of the trial, results will be prepared for presentation and publication in scientific journals.

## Discussion

With the increasing demand for TKA, further research must explore safe, optimal, cost-effective alternatives for physical rehabilitation following TKA. This single-blinded RCT will compare safety, efficacy and cost-effectiveness of a novel home-based approach, the Maxm Skate rehabilitation program to standard rehabilitative care following TKA.

### Study limitations

As is well discussed in the literature, there is potential for single-centre studies to have limited external validity. In the case of the present study, this may be considered a limitation given the enrolment of privately insured patients and the rehabilitation pathways offered to them in isolation, as compared to the rehabilitation pathways that may be available or typically selected in public healthcare centres. As such, in this study we are only capable of capturing the postoperative rehabilitation pathways that are routinely selected at Flinders Private Hospital. Interestingly, in Australia the mean discharge of privately insured TKA and THA patients to inpatient rehabilitation facilities is 40.1%, compared to 20% in public patients [41]. As such, this study will capture the frequency, length and type of rehabilitation the study participants receive, in the hopes of improving transparency and generalisability of care. In addition, the study will also be recruiting a single surgeon’s patients, which once again may reduce generalisability across surgeons within and across centres. Despite this, in order to reduce any potential bias associated with a single surgeon’s patient cohort, the study orthopaedic surgeon is to be completely blinded to treatment allocation and, wherever possible, blinded to study participation altogether. Previous studies have addressed the heterogeneity of standard care options for rehabilitation between private hospitals in Australia [42] and this also presents in our study as a potential limitation. Further to this, there may also be a deal of heterogeneity across the Maxm Skate group participants, as despite their allocation and use of the Maxm Skate exercise program, should they feel it necessary to receive additional physiotherapy to assist in their recovery, they are able to do so. These variations in rehabilitative care are unavoidable to provide equal and consistent clinical care opportunities across all patients. In order to account for such heterogeneity in the rehabilitative pathway, a clear outline of the frequency, duration and type of treatment received by each participant will be documented at each follow-up visit with the Study Coordinator. Furthermore, at study conclusion, per-protocol analyses will be performed within the Maxm Skate group to distinguish any differences observed between participants receiving any physiotherapy care additional to the Maxm Skate exercise program. Such ‘as-treated’ grouping may assist in addressing the recognised limitation of participant receipt of additional care masking any potential benefit of the Maxm Skate exercise program. Despite the above recognised limitations of this study, we believe this RCT will provide sound evidence describing the potential differences observed over the course of different rehabilitative pathways of TKA patients in our centre.

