### Randomisation and blinding

The randomisation schedule will be prepared using numbered and sealed, opaque envelopes. Participants will be randomly allocated in a 1:1 ratio to either the ‘Maxm Skate Rehabilitation Program’ or the ‘Standard Rehabilitative Care’ group. Block randomisation in groups of four will be used to ensure balance in the two groups. Randomisation will also be stratified by gender to ensure balance between groups for each gender. We note that the number of women undergoing TKA for osteoarthritis has been shown to be greater in Australia [21]. In addition, studies have demonstrated that there are differences between men and women in muscle and physical function recovery after TKA [22, 23].

The study will be single-blinded with blinding of study investigators but not participants. Participant randomisation to either Maxm Skate or Standard Care will be performed by the unblinded Study Coordinator, who will hold the treatment allocation code in confidence. The statistician will be blinded to the treatment allocation code when performing all analyses. Functional evaluations and performance tests will be conducted by a trained physiotherapist ([name]) who will be blinded to group allocation. This blinded physiotherapist will conduct all functional evaluations, excluding postoperative day 2, due to practical constraints. Non-blinded ward-based physiotherapists will conduct the day 2 assessments, as well as the preoperative Maxm Skate education session for participants allocated to the Maxm Skate group.

Due to the nature of the intervention there is a potential for participants to disclose, or physiotherapist to gauge, which group the participants are assigned. Participants will be educated and instructed not to advise the physiotherapist or treating surgeon of their group assignment at the time of their consent and randomisation with the unblinded Study Coordinator. However, if participants are concerned about their rehabilitative progress and feel it is necessary to discuss this with their treating surgeon, they will be able to do so. The breaking of blinding will be collected and reviewed during data analysis.

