##### Postoperative outpatient phase

Following the inpatient program, participants in the Maxm Skate program will only receive rehabilitation provided through the Maxm Skate program, described in the *Maxm Skate Rehabilitation Guide* (see Additional file 1). This program includes functional assessment checks at two weeks and six weeks at the participant’s home. This will ensure participants are fit to progress through from Stage One to Stage Two and from Stage Two to Stage Three of the program. Additional functional checks will be conducted if required, as assessed by hospital staff at discharge from hospital. Furthermore, the checks will allow early identification of participants who are not advancing and may require additional rehabilitative support.

Participants that are identified as requiring additional physiotherapy will receive such treatment, as required. Participant functional progress will also be assessed by the orthopaedic surgeon at the six-week orthopaedic follow-up appointment. Any additional outpatient physiotherapy received by a participant randomised to the Maxm Skate program will be permitted and recorded in the participant study file.

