### Sample size

A sample size calculation based on achieving 90% power at two-tailed type 1 error rate of 5% identified that 110 participants (55 participants per group) would be required to detect 10° of difference in ROM between the Maxm Skate program and standard care groups at three months after TKA assuming a within-group SD of 16°. The clinically significant difference in ROM of 10° and SD was estimated from parameters described by Mockford et al. [16], in which the effect of a physiotherapy regimen on ROM was measured over a one-year, post-TKA follow-up period. Furthermore, it is well established that daily activities, including climbing stairs and standing from a chair, require 90–120° of flexion, kneeling and squatting 110–165°, and 135° of flexion to lift from a bath [7–9]. However, patients rarely achieve > 120° of flexion post TKA and 110° of flexion is an optimal goal for rehabilitation following TKA [9–11]. Based on such awareness of requirements for daily activities, a 10° difference in ROM may delineate between the ability to climb stairs or kneel down in TKA patients.

In order to account for a potential 5% loss to follow-up, a total sample of 116 participants (58 per group) will be recruited.

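### The planned within-Skate comparison by receipt of extra physiotherapy is confounded by indication, has no standard-care comparator, and cannot reveal a masked Skate benefit

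*Protocol article*

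**What the plan says.** The Study limitations section commits to an analysis inside one arm: "per-protocol analyses will be performed within the Maxm Skate group to distinguish any differences observed between participants receiving any physiotherapy care additional" to the Skate exercises. It calls the same grouping both *per-protocol* and *as-treated*, and says that it "may assist in addressing the recognised limitation of participant receipt of additional care masking any potential benefit" of the Skate program.

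The Postoperative outpatient phase section explains who gets extra physiotherapy. Home checks take place at two and six weeks, and "the checks will allow early identification of participants who are not advancing and may require additional rehabilitative support". Participants found to need more physiotherapy receive it. Any additional outpatient physiotherapy is permitted and recorded. Study limitations adds a second route: participants may also obtain it if they themselves feel the need.

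The Statistical methods section puts the analyses on an intention-to-treat basis. It accounts for baseline characteristics in a sensitivity analysis. It does not mention the within-Skate contrast.

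**The concern.** Three features of the contrast do not fit its stated aim.

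- **No comparator.** Both subgroups were allocated to the Skate. A difference between them says nothing about Skate versus standard care, whichever way it falls.
- **Selection after randomisation.** The split depends on an event that follows early progress and comes before three-month ROM is measured. The article names masking as the problem to solve but not confounding by indication. Baseline values do not capture postoperative progress, so the baseline adjustment elsewhere in the plan would not remove the confounding.
- **Labels.** One grouping carries two names with different usual meanings. *Per-protocol* fits poorly, because extra physiotherapy is allowed and receiving it is not a deviation. *As-treated* would normally regroup participants across arms, which is not planned.

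The rationale invites readers to use this contrast when the intention-to-treat result is null, since its declared role is to address a benefit that extra care may have hidden. A gap produced by selection could then be taken as support for the device.

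**Working it through.** **1. The plan's own figure.** The article gives no figure for the within-Skate contrast, so the check starts from the Sample size section. Inputs: 90% power, two-sided 5% error, a 10° difference, "assuming a within-group SD of 16" degrees, and participants "randomly allocated in a 1:1 ratio".

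- Normal approximation: n = 2 × 16² × (1.960 + 1.282)² / 10² = 53.8, so 54 per group.
- Exact two-sample t-test: 54.8, so 55 per group, 110 in total.
- With 5% loss: 110 / 0.95 = 115.8, so 116, or 58 per group.

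The stated sample size reproduces and is not at issue. It supplies the SD (16°), the yardstick (10°) and about 55 evaluable Skate participants.

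**2. Model for the selection gap.** Let early progress and three-month ROM be bivariate normal with correlation r, and ROM SD 16°. The fraction f with the worst progress receives extra physiotherapy, and nothing has any effect on ROM. Both r and f are assumptions, because the article gives neither. With c = z(f) and φ the standard normal density:

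gap (Skate only minus Skate plus physiotherapy) = 16 × r × [φ(c)/f + φ(c)/(1 − f)]

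Worked case, f = 30%: c = −0.524 and φ(c) = 0.3477. Then 0.3477/0.3 = 1.159 and 0.3477/0.7 = 0.497, which sum to 1.656 SD.

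- r = 0.3: 16 × 0.3 × 1.656 = 7.9°
- r = 0.5: 16 × 0.5 × 1.656 = 13.2°
- r = 0.7: 16 × 0.7 × 1.656 = 18.5°

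**3. Range.** The first figure is for strict selection of the worst fraction. The figure in brackets is for selection that follows progress half as closely (r replaced by r/2).

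| f | r = 0.3 | r = 0.5 | r = 0.7 |
|---|---|---|---|
| 10% | 9.4° (4.7°) | 15.6° (7.8°) | 21.8° (10.9°) |
| 20% | 8.4° (4.2°) | 14.0° (7.0°) | 19.6° (9.8°) |
| 30% | 7.9° (4.0°) | 13.2° (6.6°) | 18.5° (9.3°) |
| 50% | 7.7° (3.8°) | 12.8° (6.4°) | 17.9° (8.9°) |

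**4. Nominal significance.** With 55 Skate participants, strict selection and no treatment effect, a 5% t-test between the subgroups rejected in 25% (r = 0.3, f = 10%) to 99.8% (r = 0.7, f = 50%) of simulated trials (4,000 runs per scenario).

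**5. Sign.** If extra physiotherapy truly helps, its effect is subtracted from the gap.

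- Strict selection, r = 0.3, f = 50%, true benefit 10°: 7.7 − 10 = −2.3°.
- Looser selection, same r and f, true benefit 5°: 3.8 − 5 = −1.2°.

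The contrast mixes selection with any physiotherapy effect and cannot separate them.

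**The case against.** The strongest reply is that this is one supplementary analysis in a limitations section, worded cautiously, and that the primary comparison is untouched. Much of the surrounding text speaks of describing care pathways, which is already the acceptable use. Modelling details may sit in an analysis plan that is not shown. All of this stands, and it limits the weight of the point. It does not rescue the stated purpose: the article itself says that the grouping may help with masking, and no covariate adjustment can supply the missing standard-care comparator.

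A reader might go further and infer that the analysis is bound to show a false Skate benefit, or that the Skate-only subgroup is faster-recovering by construction. The documents do not support that. Some extra physiotherapy is self-chosen and need not follow measured progress, so selection is partial. Strict allocation to the worst fraction is close to a worst case. A real physiotherapy effect could shrink or reverse the gap. The Background does report a meta-analysis finding no ROM difference between clinic-based outpatient physiotherapy and unsupervised home exercise, which makes a gap favouring Skate-only participants the likelier outcome, but not a certain one.

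A reader might also suppose that Skate-only participants will be set against the whole standard-care arm. The article plans no such comparison, so no bias is claimed for it here.

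**Conclusion.** The point holds. Followed exactly as written, the contrast cannot do what the article says it may do: it has no standard-care comparator and is confounded by indication. Its likely direction favours Skate-only participants.

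On the assumed inputs, the gap from selection alone runs from about 4° (looser selection) to about 22° (strict selection), so it can approach or exceed the 10° target. These sizes illustrate and do not predict, since they rest on assumed values of f and r, a normal model and no treatment effect. That the contrast is uninformative about the Skate rests on the design alone and needs none of these assumptions.

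The randomised intention-to-treat comparison of three-month ROM is unaffected.

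**What to change.** In Study limitations:

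1. Remove the *per-protocol* and *as-treated* labels from this grouping.
2. Remove the claim that it addresses masking of a Skate benefit.
3. State instead that outcomes in the Skate arm will be described by receipt of additional physiotherapy, that receipt depends partly on early progress, and that no inference on Skate efficacy will be drawn from the contrast.

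This is a wording change. It needs no new data and gives up no valid inference.

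**Optional.** If the effect without extra physiotherapy is of real interest, any such analysis should keep the randomised standard-care arm as comparator, treat early progress (ROM and pain at the early visits) as a time-varying confounder, for example by inverse-probability weighting, and be labelled supplementary. Its costs are real:

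- **Precision.** At an assumed 30%, only about 16 or 17 of 55 Skate participants would have extra physiotherapy, so precision would be low and weights could be unstable.
- **Timing.** ROM at four or six weeks is already post-treatment for anyone who starts after the two-week check. The analysis therefore needs a recorded start date for the extra care. The article lists frequency, duration and type of treatment but no start date.
- **Assumption.** It requires no unmeasured confounding, and a participant's own sense of needing help is a likely unmeasured driver.

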## Abbreviations

AE: Adverse event
App: iOS Application
AR-DRG: Australian Bureau of Statistics and Australian Refined Diagnosis Related Groups
CRF: Case Report Form
EQ – 5D 5L: Euroqol 5 Dimensional Health Survey – Level 5
FPH: Flinders Private Hospital
iOS: iPhone Operating System
KOOS: Knee Injury and Osteoarthritis Outcome Score
MVIC: Maximum voluntary isometric contraction
OARSI: Osteoarthritis Research Society International
OKS: Oxford Knee Score
PASS: Patient Acceptable Symptom State
QALY: Quality-adjusted life year
RCT: Randomised controlled trial
ROM: Range of motion
TKA: Total knee arthroplasty
UK: United Kingdom
VAS – Pain: Visual Analogue Scale for Pain
